## Methods and analysis

### Study design

This study protocol is a two-arm double-blind prospective RCT comparing a web-based psychoeducational intervention to a waiting control condition among adults in stepfamilies (*N* = 112). The proposed intervention consists of a three-module (Figure 1) interactive Game that lasts a minimum of 30 and a maximum 60 min and can be played over the course of 1 month in computer. Modules are sequential and focus on the romantic relationship, co-parenting and step-parenting. Assessments are made before (*T_0_*) and 1 month after the intervention (*T_1_*). The experimental group (EG) has a second follow-up after 2 months (*T_2_*). The control group (CG) is on a waiting list until completion of *T_1_*, and then gets access to the intervention. Intervention and measurements are carried out online. The protocol uses the learning app H5P and *Limesurvey* survey design tool integrated into Moodle e-learning management system. The use of H5P interactive teaching aids to solve problems has been studied in literature as an important tool for educational context (Wang et al., 2016; Sinnayah et al., 2021). Figure 2 displays the study schedule of enrollment, interventions and assessments. This RCT will follow the SPIRIT guidelines (Chan et al., 2013a, 2013b) and the CONSORT statement (Moher et al., 2010; Schulz et al., 2010).

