### Instruments and measures

A sociodemographic questionnaire will be used at *T_0_* to describe the sample and compare groups. Primary and secondary outcome measures administered at *T_0_* and *T_1_* will assess intervention efficacy and changes in marital quality, remarriage beliefs, co-parenting and stepparenting attitudes, and family functioning. Stability of these changes is assessed at *T_2_* for those in the EG. Specific outcomes related to the quality of the intervention and perceptions of intervention benefits will be accessed after the intervention for participants in the experimental condition group.

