**Figure 4 fig4:**
[figure not shown]
Branching scenario from Scene 10 of Module 2-“Stepparenting.”

*Wait-list*. After replying to the baseline questionnaire (*T_0_*), participants assigned to this condition receive a message informing that they are on the waiting list to participate on the course. The wait-list CG is also notified that they will be receiving further instructions in 1 month, and that access to the course is be possible after replying to a second assessment (*T_1_*).

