## Data and statistical proposed analysis

Data will be analyzed using the Statistical Package for Social Sciences (SPSS), v.24 (IBM Corp, 2016). Preliminary and descriptive statistics will be conducted to describe the sociodemographic characteristics of the participants, standard deviations (SDs) and data normality. Missing data will be manage through intention-to-treat analysis (ITT). The Chi-square (*χ*^2^) and the independent sample *t*-test will be used to detect significant differences between the EG and CG on the *T_0_* sociodemographic characteristics and psychosocial variables. To explore the effect of the intervention on psychosocial variables and intervention perceived benefits, researchers will conduct repeated measures mixed ANOVAs to analyze the interaction between groups (EG and CG) and time (baseline, post-test and follow-up for EG; baseline and post-test for CG). To analyze the main effects, *post hoc* tests using Bonferroni correction will be performed. The independent *t* test will be used to compare how satisfied the EG and the CG are with the psychoeducational simulation Game on the post-intervention assessment (*T_1_*).

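### The planned EG-versus-CG comparison of satisfaction at T1 has no valid control ratings, and perceived benefits sit in a group-by-time ANOVA for which the text plans no baseline or control values

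*Protocol article*

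**What the plan says.** Two sentences in the protocol article, Data and statistical proposed analysis, are at issue.

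- **Satisfaction.** An independent t test is planned that "will be used to compare how satisfied the EG and the CG are with the psychoeducational simulation Game on the post-intervention assessment", which the sentence labels T1.
- **Perceived benefits.** "To explore the effect of the intervention on psychosocial variables and intervention perceived benefits, researchers will conduct repeated measures mixed ANOVAs" to examine group by time. The time points are given as "baseline, post-test and follow-up for EG; baseline and post-test for CG".

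Other sections fix who has used the Game and who answers these scales.

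- **Study design:** CG "is on a waiting list until completion of" T1, "and then gets access to the intervention".
- **Wait-list paragraph (under GSteps development):** for CG, "access to the course is be possible after replying to a second assessment", again T1.
- **Instruments and measures:** outcomes on the quality of the intervention and its perceived benefits "will be accessed after the intervention for participants in the experimental condition group".
- **Feasibility measures:** the Program Satisfaction Scale (PSS) rates satisfaction with the programme in three parts: usability, content and parenting impact. The Intervention Perceived Benefit scale (IPB) has twelve agreement items on what was learned, taken once the intervention is over.

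**The concern.** The t test needs ratings of the Game from people who, by design, have not yet opened it. The ANOVA needs baseline and control values of a scale that the text assigns to EG after the intervention. Both sentences appear to treat PSS and IPB like the efficacy scales, which both arms complete at T0 and T1.

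Feasibility is a stated aim alongside efficacy, and satisfaction and knowledge learned are named outcomes in the abstract. The Discussion also lists knowledge learned among the results that would count towards evidence of efficacy. If the analysis sentences stay as they are, the team will have to abandon two announced analyses after the data are in, or improvise data to fill them.

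**Working it through.** The document gives no figure to reproduce. The check sets the analysis sentences against the data that the text plans to collect.

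**1. Satisfaction at T1**

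The t test compares mean(EG, T1) with mean(CG, T1), and its standard error contains a term s²/n for CG. The n that matters is the number of CG participants who have used the Game when they answer T1.

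- Study design and the wait-list paragraph both make CG access depend on completing T1, not on a calendar date. The result therefore does not depend on when T1 falls.
- Valid CG ratings at T1 = 0.
- The denominator does not matter. Planned enrolment is 112 / 2 = 56 per arm. If the roughly 50% dropout cited under Power analysis applied evenly, about 56 × 0.5 = 28 CG participants would answer T1. The valid count is zero of either number.
- PSS cannot be answered meaningfully without exposure. Its usability part asks how hard or easy the programme was, and the other parts ask about its content and its effect on parenting.
- A later CG rating would not be the stated test. The sentence fixes T1, CG has only baseline and post-test in the analysis plan, T2 is for EG, and no CG assessment after delayed access is described.

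**2. Perceived benefits in the mixed ANOVA**

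The analysis section lists five group-by-time cells. Against these, the text plans IPB as follows:

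| Group | T0 | T1 | T2 |
|---|---|---|---|
| EG | in model; IPB not planned | in model; IPB planned | in model; IPB not excluded |
| CG | in model; IPB not planned | in model; IPB not planned | not in model |

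The group-by-time effect from T0 to T1 is

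[mean(EG, T1) − mean(EG, T0)] − [mean(CG, T1) − mean(CG, T0)].

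Only the first of its four terms is clearly planned. Without the other three, the following cannot be estimated:

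- the EG change from baseline, which needs EG at T0;
- the group difference at T1, which needs CG at T1;
- the interaction, which needs all four.

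If IPB were also taken in EG at T2, that would add a T1-to-T2 change within EG but no comparison between groups.

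**The case against.** The best defence concerns the second half. Instruments and measures assigns these outcomes to EG after the intervention, but it does not expressly forbid other uses. IPB is described as knowledge learned, with agreement items built on the Game's content. Such items might be answerable by people who have not played, and a group-by-time model would then be computable. The items (Appendix C) and the assessment schedule (Figure 2) are not shown. This stands as a limit: the text shows a contradiction between sections, not that IPB could never be given at baseline or to CG. It does not remove the contradiction, because the analysis section would still rely on data that the measures sections do not plan.

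A reader might also infer that a spurious EG–CG difference will be reported, because CG would be sent forms about a programme it has not used. Nothing in the document plans that. If the forms are not sent, the satisfaction test simply cannot be run. The risk arises only if someone tries to fill the gap.

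It can also be said that these are neither primary nor secondary outcomes, and that the third feasibility component, the open question put to six EG participants, is untouched. Both points are correct and bear on severity.

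The satisfaction half has no comparable defence: the sentence names CG, the Game and T1.

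**Conclusion.** The point holds, with different strength in its two halves.

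- **Satisfaction:** the test cannot be validly run as written. Valid CG ratings at T1 are zero. This rests only on the access rule, which is stated twice, and on PSS being a rating of the programme.
- **Perceived benefits:** as the text stands, no baseline or CG values are planned and the interaction cannot be estimated. One of the four cells needed for the T0-to-T1 contrast is clearly planned. This assumes that the unseen schedule figure agrees with Instruments and measures and with Feasibility measures.

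A reader might go further and conclude that no feasibility analysis is possible or that the efficacy results are compromised. Neither follows. EG-only description of both scales remains available, the qualitative component is unaffected, and dyadic adjustment, marital social skills and the secondary scales do not depend on PSS or IPB. The severity is should-fix.

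**What to change.** 1. Delete the EG-versus-CG t test of satisfaction. Replace it with descriptive summaries in EG after the intervention, for example mean, SD and 95% CI for each PSS subscale, with the number responding.
2. Remove perceived benefits from the mixed ANOVA sentence and report IPB descriptively for EG. The alternative is to keep it in the model, but only if the items can be answered without having played, and if Instruments and measures and Feasibility measures are changed to give IPB to both arms at T0 and T1.
3. If CG satisfaction is of interest, collect it only after CG has used the Game and report it descriptively.

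Item 1 and the main option in item 2 cost only wording. Keeping IPB in the model would add twelve items at T0 in both arms and at T1 in CG. Item 3 would add one existing online form, sent to CG after its access period.

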### Power analysis

G*Power (Faul et al., 2007) was used to calculate a minimum sample size. To test the efficacy of the intervention compared with the control condition, we propose a power analysis based on a probability level of 0.05 and a power of 0.80 (Hawkins et al., 2008; Lucier-Greer and Adler-Baeder, 2012). For analysis of covariance (ANCOVA), G*Power indicated an entire sample of 74 to detect a medium effect size of *d* = 0.5. However, a high dropout rate (about 50%; Wangberg et al., 2008) is usually encountered in internet-based interventions and thus we ultimately plan for a sample of 112 participants (56 participants per condition).

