## Procedure

### Recruitment and randomization

*GSteps* can be called an intervention, psychoeducational activity, or “Game.” Recruitment will be announced in social media (i.e., Facebook, Instagram, Self-help forums) or through a project website. On all these platforms, a link to an online questionnaire (*T_0_* – pre-test assessment) should be available. Participants meeting inclusion criteria and consenting to enter the study proceed and complete the pre-test questionnaire. After that, an automatic equation set will randomly (1:1) allocate participants to the EG or to the CG. Based on the random assignment, an automatic message is sent. Participants in the EG are invited to play *GSteps* and receive an email with a link and a confidential username and password. Participants allocated in CG receive an email informing them that they are on the waiting list. Both participants and the research team will be blind to the assignment.

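### The total of 74 for ANCOVA at d = 0.5 does not follow from the stated inputs, which give 128

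*Protocol article*

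**What the plan says.** The Power analysis section names G*Power and fixes "a probability level of 0.05 and a power of 0.80". It then says that, for ANCOVA, G*Power "indicated an entire sample of 74 to detect a medium effect size of" d = 0.5. Because "a high dropout rate (about 50%; Wangberg et al., 2008) is usually encountered in internet-based interventions", the plan is raised from 74 to 112, or 56 per arm.

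The other inputs come from elsewhere in the article. Study design describes a "two-arm double-blind prospective RCT comparing a web-based psychoeducational intervention to a waiting control condition". Recruitment and randomization says that "an automatic equation set will randomly (1:1) allocate participants to the EG or to the CG".

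The article states no sidedness, number of covariates, share of variance explained by a covariate, or correlation between baseline and outcome.

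**The concern.** Test, alpha, power, effect size, number of arms and allocation ratio are all printed, and together they determine a sample size. For a two-arm comparison at d = 0.5 with 80% power, a statistician expects about 64 per arm. The article has 37 per arm (74 / 2) without naming anything that would account for the reduction.

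The figure carries weight. It is the base for 112 and 56 per arm; 112 is called the minimum required sample size in the Abstract and is given as N in Study design. If 74 really corresponds to a larger effect, the trial has less than its stated power for the effect it names, and a null result would be read as stronger evidence against a medium effect than it is.

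**Working it through.** **Inputs.** Alpha 0.05, power 0.80, d = 0.5, ANCOVA (Power analysis); two arms (Study design); 1:1 allocation (Recruitment and randomization). Taken as assumptions because they are not stated: a two-sided test, which is what the ANCOVA F test is, and one covariate.

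**Formula.** For two equal groups f = d/2 = 0.25. The group test has numerator df 1 and denominator df N − 2 − 1 = N − 3. The noncentrality is λ = f²N = 0.0625·N. Power is the probability that a noncentral F with these values exceeds the 5% critical value of the central F.

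**Attempt to reproduce 74.**

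| N analysed | λ | Power at d = 0.5, no covariate gain |
|---|---|---|
| 56 | 3.500 | 0.451 |
| 74 | 4.625 | 0.564 |
| 112 | 7.000 | 0.746 |
| 127 | 7.938 | 0.798 |
| 128 | 8.000 | 0.801 |

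The first total to reach 0.80 is 128. Two or three covariates also give 128, as does the two-sided t-test; the normal approximation gives 126. The stated 74 is 54 participants short (128 − 74).

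**What would give 74.**

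- *A larger effect.* Solving for 80% power at N = 74 gives f = 0.330, so d = 2 × 0.330 = 0.66.
- *A baseline correlation r.* Adjusting for baseline shrinks the residual SD by √(1 − r²), so the effective f is 0.25/√(1 − r²). Setting this to 0.330 gives r = √(1 − (0.25/0.330)²) = 0.65.
- *A one-sided test at 0.05.* Without covariate gain this needs 102 (power 0.806), and 74 gives 0.69. It reaches 74 only with a correlation of about 0.52 as well.
- *Other routes.* One-sided alpha of 0.10 gives 74, but the article says 0.05. Entering d as f (f = 0.5) with numerator df 10 gives 74, but a two-arm comparison has numerator df 1, and then f = 0.5 gives 34.
- *Repeated-measures interaction F test, f = 0.25, two time points.* This gives 65 at correlation 0 and 34 at 0.5, so neither matches 74.

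No reading that uses only the printed inputs returns 74.

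**Sensitivity to an assumed correlation (d = 0.5, two-sided, one covariate).**

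| r | Effective f | N for 80% | Power at 74 | Power at 112 |
|---|---|---|---|---|
| 0 | 0.250 | 128 | 56% | 75% |
| 0.4 | 0.273 | 108 | 64% | 82% |
| 0.5 | 0.289 | 97 | 69% | 86% |
| 0.6 | 0.313 | 83 | 76% | 91% |
| 0.65 | 0.329 | 75 | 80% | 93% |
| 0.7 | 0.350 | 67 | 84% | 96% |

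N in this table is the smallest total, without rounding to equal arms. At r = 0.65 exactly the total is 75; the solved value for 74 is 0.653.

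**The case against.** The best defence is that 128 is the case in which the covariate contributes nothing, whereas the usual reason for ANCOVA is to use the baseline value. The outcomes are measured at T0 and T1, and a correlation near 0.65 is plausible for a repeated scale. On that view 74 may be a sound number with one input left out of a condensed article. This stands in part: an arithmetic slip is not proven, and 74 is defensible for ANCOVA if that correlation was assumed and can be sourced. It does not rescue the sentence as printed. The G*Power ANCOVA routine takes an effect size f, so a correlation has to be built into f by the user; the value entered would then have been about 0.33, not the 0.25 that d = 0.5 implies. The result also depends heavily on the missing input: power at 74 runs from 69% at r = 0.5 to 84% at r = 0.7.

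A second objection is that 112 will be enrolled, so the shortfall is absorbed. With 112 analysed and r of at least 0.4, power does pass 80%. But the article itself expects about 50% dropout, and with no covariate gain even all 112 give 75%. The 45% at 56 analysed combines this problem with the size of the dropout allowance, which is a separate matter, and an intention-to-treat analysis might retain more than 56.

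Third, the explanations above are examples, since other unstated settings also land near 74. That is correct, and it is a further reason to print the settings used.

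**Conclusion.** The concern holds. With two equal arms, alpha 0.05 two-sided, 80% power and d = 0.5, ANCOVA needs 128 unless a covariate gain is assumed, and the article states none. At 74 the power for d = 0.5 is 56% without such a gain, and the effect detectable with 80% power is d = 0.66. A baseline correlation of about 0.65 would reconcile 74 with d = 0.5.

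The conclusion does not hinge on the two-sided assumption, because one-sided 0.05 still needs 102. What is established is that the stated sample size and power do not follow from the stated inputs. Which unstated setting produced 74 cannot be determined from the article.

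**What to change.** Restate the calculation with the settings that were actually entered in G*Power: f, sidedness, numerator df, number of covariates and any assumed correlation. Then one of three statements applies.

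1. If an f of about 0.33 was entered as the effect itself, state the detectable effect as d of about 0.66 instead of 0.5.
2. If d = 0.5 was combined with an assumed T0–T1 correlation of about 0.65, state that correlation and its source, and give power at correlations of 0.5 and 0.7 (69% and 84% at 74).
3. If no correlation was assumed, report 128 as the total for d = 0.5, and give the power of the planned enrolment (75% if all 112 are analysed).

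The first two should be used only if they describe what was done; values solved backwards from 74 are not a justification.

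The restated calculation should also match the planned test. The Data and statistical proposed analysis section plans a mixed-ANOVA group-by-time interaction. With two time points this compares change scores, with variance factor 2(1 − r). For d = 0.5 it needs 128 at r = 0.5 and 90 at r = 0.65, so a correlation of 0.65 would support 74 for ANCOVA but not for that test.

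The cost is one re-run of G*Power and one reworded paragraph, with no extra enrolment. Under options 1 and 3 the stated figure becomes less favourable.

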**Methods/design:**

A RCT design is presented to evaluate the outcomes of a self-administered, interactive and web-based psychoeducational Game targeting dyadic marital adjustment and interpersonal skills as the primary outcomes and remarriage beliefs, family function and stepparenting and co-parenting attitudes as the secondary outcomes. Other outcome measures include satisfaction with *GSteps*, participants’ knowledge learned after the intervention and a purposive sampling method will be used to access feasibility. The minimum required sample size is 112 participants (56 per condition) randomly allocated either to an experimental group (EG), receiving *GSteps* intervention, or to a wait-list control group (CG). A survey is conducted electronically. Assessments take place at baseline (*T_0_*), after the intervention (*T_1_*) and 1-month follow-up (*T_2_*).

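### The planned 112 does not cover the stated 50% dropout: it leaves 56 analysable participants, 18 fewer than the 74 the plan says it needs for 80% power

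*Protocol article*

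**What the plan says.** The Power analysis section, under Data and statistical proposed analysis, sets out the sample size in three steps.

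- **Targets:** "a probability level of 0.05 and a power of 0.80".
- **Analysed sample needed:** for an ANCOVA, "G*Power indicated an entire sample of 74 to detect a medium effect size", with the effect given as d = 0.5.
- **Allowance for loss:** it cites "a high dropout rate (about 50"%) as usual for internet-based interventions, and from this concludes "thus we ultimately plan for a sample of 112 participants (56 participants per condition").

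The abstract (Methods/design) repeats the result without its derivation: "The minimum required sample size is 112 participants (56 per condition"), randomly allocated to the two arms.

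Under Recruitment and randomization, allocation follows completion of the baseline questionnaire, so any later loss comes out of the 112.

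**The concern.** The plan raises 74 to 112 explicitly because of the 50% dropout rate, so a reader will take 112 as the number that still leaves 74 after that loss. It leaves 56. The stated 80% power is then not secured under the plan's own expectation, and the abstract gives the reader no way to see this. If the trial finds no difference on marital adjustment or marital social skills, the result could be taken as evidence that the Game does not work when the trial had a lower chance of detecting the assumed effect than its protocol claims.

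**Working it through.** **Inputs** (all from Power analysis): analysed sample needed 74; dropout 0.50; planned sample 112 (56 per arm); alpha 0.05; power 0.80; d = 0.5. The number of sides of the test is not stated; two-sided is assumed below.

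**Reproducing 112.** The article does not show the inflation step. Two forms were tried:

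- n × (1 + dropout) = 74 × 1.5 = 111, rounded up to an even number for two equal arms = 112. This matches.
- n / (1 − dropout) = 74 / 0.5 = 148. This does not match.

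The second form keeps 74 after a 50% loss. The first adds half of 74 to the sample but then loses half of the enlarged sample.

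**What 112 delivers.**

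- Analysable at 50% dropout: 112 × 0.5 = 56 (28 per arm). Shortfall: 74 − 56 = 18.
- Largest dropout at which 74 remain: 1 − 74/112 = 0.339, about 34%.

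**Power on the plan's own premise.** For two groups and one covariate, the test is a noncentral F with df1 = 1, df2 = N − 3 and noncentrality f²N. The f that gives exactly 80% power at N = 74 is 0.330. Holding that f fixed:

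| Dropout | Analysed | Power |
|---|---|---|
| 20% | 90 | 0.87 |
| 30% | 78 | 0.82 |
| 34% | 74 | 0.80 |
| 40% | 67 | 0.76 |
| 50% | 56 | 0.68 |

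**Detectable effect at 56 analysed, 80% power.** The required f is 0.381.

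- With no gain from the covariate, d = 2 × 0.381 = 0.76.
- With the covariate gain implied if d = 0.5 needs only 74, d = 0.5 × 0.381/0.330 = 0.58.

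**How far this depends on the 74.** For two groups, d = 0.5 corresponds to f = 0.25. With no covariate gain, 80% power needs N = 128, not 74. To reach about 74 with d = 0.5 takes a baseline–outcome correlation of about 0.65, since 0.25/√(1 − 0.653²) = 0.330; the article does not state one. With no covariate gain, power is 0.75 at 112, 0.56 at 74 and 0.45 at 56. Of the fall from 0.80 to 0.45, about 0.24 therefore comes from 74 being too few on that assumption, and about 0.11 from the drop from 74 to 56. If 128 were the true need, 50% dropout would call for 128/0.5 = 256.

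**The case against.** The strongest reply is that the 50% may describe people leaving the intervention, not missing outcomes in both arms. The Strengths and limitations section lists dropout during the intervention and missing follow-up data as separate things. The wait-list arm has no intervention to leave before T1, and it gains access to the course only after answering T1, which encourages response. If only the experimental arm lost half, 28 and 56 would remain. That carries the information of a balanced total of 4 × 28 × 56/84 = 74.7, and power on the plan's premise would be about 0.805. The arithmetic is right, but the article does not state this rationale. It applies one rate to move from the whole required sample to the whole planned sample.

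Other points against:

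- **Intention-to-treat is planned.** It is named with no method attached, and naming it does not restore outcomes that were never collected. If it removed the need for an allowance, there would have been no reason to raise 74.
- **112 is called a minimum, so more may be recruited.** This is so, but the minimum is the figure offered as sufficient.
- **The ×1.5 step is not written in the article.** This stands; it is an inference. The shortfall follows from 112, 50% and 74 alone.
- **The 68% and the 148 both accept a 74 that the stated inputs alone do not reproduce.** This also stands, and both figures must carry that condition. Doubt about the 74 makes the shortfall larger, not smaller.

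**Conclusion.** The concern holds. The planned sample contradicts the inputs given for it: at 50% loss, 112 leaves 56 against a stated need of 74, and the number consistent with those inputs is 148. Accepting the plan's claim that 74 gives 80% power, actual power at 50% dropout is about 68%. For d = 0.5 with no covariate gain it is about 45%, but most of that deficit comes from the 74 and not from the dropout step.

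The conclusion assumes that the 50% means loss of analysable participants across both arms, which is how the Power analysis section uses it. The power figures further assume a two-sided test at 0.05 and an ANCOVA with one covariate. Whether 74 is itself right is a separate question.

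**What to change.** Correct the Power analysis section and the Methods/design part of the abstract together.

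1. State that 112 randomised keeps 74 analysable, and hence the planned 80% power, only up to about 34% dropout.
2. State that at the expected 50% dropout 56 are analysed, with about 68% power if 74 gives 80%, and give the detectable effect at 56 with its covariate assumption (d of about 0.76 with no covariate gain).
3. Remove the description of 112 as the minimum, or give 148 as the number that matches 50% dropout, noting that it takes the 74 as given.
4. If the 50% was meant for one arm only, or for leaving the intervention and not for missing T1, say so and show the inflation step on that basis.

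Confirm how the 74 was obtained before printing any figure that depends on it. The cost is rewording in two places and a less favourable power statement. No added recruitment is needed for the text to be correct; reaching 148 would be a separate decision for the sponsor.
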